### Interventions

#### Intervention group: parent-administered pediatric tuina

Children in the intervention group will receive parent-administered pediatric tuina during the treatment period. Figure 3 presents the intervention implementation procedure. The parents will attend an online training program (2 training sessions, 5 h in total) to gain the knowledge and basic manipulations of pediatric *tuina* on ADHD symptoms in preschoolers. Contents of the training sessions will cover the manipulations and acupoints that are commonly used in treating ADHD. The instructor will, inspect their practice, and make feedback to them if there is any deviation. At the end of the training sessions, to assess the parents’ mastery of the contents and techniques, the parents will be asked to conduct the manipulations in the prescription (see Additional file 3) in front of the TCM practitioner via online video chat, or take a video of the manipulations in the prescription and submit it to the TCM practitioner for an assessment. Parents who have passed the assessment could the start conducting the intervention at home, while for those who have not passed, they will be asked to receive the training for one more time until they could appropriately conduct the manipulations. Then they will deliver the *tuina* on their child at home in the following 2 months according to the *tuina* prescriptions formulated by the TCM practitioner. The *tuina* prescriptions will comprise the acupoints selected, the corresponding manipulation, conduction frequency, times of each manipulation, and other necessary information. The parents will be told to deliver pediatric *tuina* therapy on their children every other day, with 20-30 min each day. A logbook will be used for recording (see Additional file 4). Videos of the manipulation techniques and relevant teaching materials will be provided to the parents via social media.

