#### Active control group: parent-child interaction training

Parents in this group will receive a parent-child interaction training program which includes progressive muscle relaxation exercise training for children and a health education booklet of ADHD and coping skills. The parents in this group will have to complete an online training session of progressive muscle relaxation exercise [39], which aims to help children reach a relaxation state by relaxing their muscles when facing stresses. The health education booklet covers the background knowledge of ADHD, suggestions, and examples of coping skills (e.g., coping skills for reaction to stress and conflict with children) and interaction skill training for parents (e.g., behavior management, self-regulation, improving organization, improving relationship, and use of encouragement) [40]. All the training contents are recommended by the Department of Health, the government of the Hong Kong Special Administrative Region. The training serves as an early intervention, with the emphasis on modifying the improper parenting methods and enhancing the positive parent-child interaction when the children are still at their preschool stage. Parents will be asked to complete an online written test after they have viewed the online training and teaching materials. They will be asked to spend at least 20 min every other day during the treatment period on doing progressive muscle relaxation exercises with their child and record their practice on a logbook (see Additional file 5).

During the study period, the children’s ongoing treatment, such as medications, behavioral therapies, and other services such as mental health service and parents-supporting activities will not be intervened in both groups. Information on their TAU will be recorded, and they will be asked not to start new treatment targeting ADHD symptoms during the study period. For subjects in both groups, they will be considered to have completed the program (completers) if they have attended the training lessons and performed the treatment at home for at least 3 days per week during the 8-week intervention period.

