## Discussion

This pilot trial aims to assess the feasibility of parent-administered pediatric *tuina* for ADHD symptoms in preschool children. There have been several studies conducted on pediatric *tuina* for ADHD; however, those studies were limited by various methodological problems such as invalidated outcomes measures, unclear randomization and allocation concealment methods, lack of appropriate control intervention to test the specific effects. To more rigorously assess the preliminary effects of pediatric *tuina*, we designed this pilot trial to overcome the limitations of previous studies.

Children in the intervention group will receive individualized *tuina* prescriptions. It might increase the complexity of the intervention and hamper the reproducibility of the intervention, but treatment individualized based on TCM pattern identification is believed to be the optimal practice of pediatric *tuina*. Our design will simulate the real-world practice of *tuina* in the clinical setting.

The pediatric *tuina* is a complex intervention based on TCM theory and past clinical experience, of which the theoretical framework is relatively less researched. Therefore, we included a process evaluation and proposed a logic model to depict the possible causal assumption and mechanism of impacts of pediatric *tuina*. This logic model will inform further fully-powered study and guide trials with similar parent-administered settings in future research.

We use parent-child interaction training as a control intervention which includes the progressive muscle relaxation exercise and health educational materials. The use of sham acupressure as a control intervention is difficult as the non-acupoint locations are not well defined [50]. This control design offers training on muscle relaxation and coping skills, and education of ADHD knowledge to the parents. Both groups contain components that aim to improve parent-child interaction, relive children’s ADHD symptoms, and enhance parents’ knowledge of ADHD. This controls the non-specific effects of pediatric *tuina* due to enhanced parent-child interactions and contacts time to the research personnel.

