We anticipate that there will be a few practical issues in performing this study. Firstly, the subjects will be provided with two consultations for TCM pattern identification (one at baseline and one at the end of first month) and the *tuina* prescription may be adjusted. However, the subjects may be more preferable to the original manipulation that they learned at the beginning as they have already mastered the manipulation and found benefit effects. In this case, we may offer them an option to continue the original manipulation. Secondly, parents usually have a great commitment to their family and their time schedule may be less flexible. Although we will inform them the schedule of the training lessons before baseline assessment, we foresee that some parents may not be able to attend all the lessons after randomization.

There are several limitations to this pilot study. First, given the nature of the intervention and the control intervention, it is impossible to blind either the parents, children, or TCM practitioners. To minimize the detection bias, the TCM practitioners would not be involved in the outcome assessment and the outcome assessors will be blinded during the process of intervention conduction and data collection. Second, although we will use MoCA to ensure that the parents have a normal cognitive function, the discrepancies in the learning abilities and education level may affect their mastery of the *tuina* technique and hence the effects of the treatment. However, it would truly reflect the implementation of the intervention in the daily clinical practice as the parents’ backgrounds usually vary. Finally, our control group did not test the *tuina’s* specific effect of exerting physical pressure on the specific body location based on meridian theory.

Our study will add to the current evidence of pediatric *tuina* for ADHD in preschool children based on meridian theory. Parent-administered pediatric *tuina* is a potential alternative therapy with fewer side effects and economic burden, and is more flexible for parents and children to receive the treatment. Our results will also inform the clinicians and practitioners about the feasibly of training the parents to administer the *tuina* technique to relieve their child’s ADHD symptoms.

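### The Discussion says the control arm accounts for contact time with research staff, but the arms as described are not matched on staff contact

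*Protocol article*

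**What the plan says.** The Discussion justifies the comparator by saying that both groups contain parent-child interaction and education components. It then says that the design controls non-specific effects of tuina "due to enhanced parent-child interactions and contacts time to the research personnel". The statement carries no qualification.

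On the tuina arm, the section on the intervention group gives "2 training sessions, 5 h in total". The instructor is to "inspect their practice, and make feedback to them if there is any deviation". Each parent then shows the prescribed manipulations "in front of the TCM practitioner via online video chat" or sends in a video for assessment, and those who do not pass are retrained until they can perform them. The Discussion adds that "the subjects will be provided with two consultations for TCM pattern identification (one at baseline and one at the end of first month"), after which the tuina prescription may change.

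On the control arm, the section on the active control group says: "The parents in this group will have to complete an online training session of progressive muscle relaxation exercise". Parents also receive a booklet and "complete an online written test after they have viewed the online training and teaching materials". No session length is given, and no observed practice, individual feedback or retraining is described.

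The section on intervention adherence offers WeChat consultation to both groups and describes researcher reminders twice a week.

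**The concern.** A comparator controls for staff attention only if both arms receive similar attention. The sections that describe the arms list components of supervised contact for tuina that have no counterpart in control, so the Discussion credits the design with a property it does not have.

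This matters because of how the outcomes are measured. The Blinding section says that parents and practitioners cannot be blinded. Parents complete SNAP, PAS, CSHQ and PSS themselves, and the blinded assessors only guide completion and collect the data. More attention from a practitioner, and the expectation that comes with it, can therefore enter the scores directly.

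The consequence reaches past the pilot. The Statistical analysis section computes a standardized between-group effect size. The Sample size section wants the pilot's confidence interval to inform later power calculations, and the same outcomes are meant for the main trial. The Discussion also faults earlier studies for lacking a control suited to testing specific effects. A reader who takes the contact-time statement at face value would regard attention as already removed from the difference.

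**Working it through.** There is no stated figure to reproduce. The check sets the described contact side by side and then asks how far the size of the gap can be fixed.

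**Step 1. Components of staff contact by arm**

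| Component | Tuina | Control | Source |
|---|---|---|---|
| Training | 2 online sessions, 5 h | 1 online session, length not stated | Intervention group; Active control group |
| Practice inspected, with feedback | Yes | Not described | same |
| Check of learning | Practitioner assesses manipulations, live or by video | Online written test | same |
| Retraining if not passed | Until competent | Not described | same |
| Baseline consultation | Yes | Unclear | Discussion; Inclusion criteria |
| Month-1 consultation | Yes | Apparently not, since it serves the tuina prescription | Discussion |
| WeChat help | Yes | Yes | Intervention adherence |
| Reminders | Yes | Apparently yes | Intervention adherence |

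No row shows more contact in the control arm. Three rows (inspected practice, practitioner assessment, retraining) favour tuina without depending on session length or on how the consultations are read.

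**Step 2. Can the gap be expressed in hours?** Only under assumptions. Let c be the length of the control session, a the live time of the skill assessment and m the length of the month-1 consultation. The baseline consultation is left out because it may reach both arms.

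Tuina contact = 5 + a + m

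Assume a = 0 to 0.5 h (0 if a video is submitted) and m = 0 to 0.5 h. Then tuina contact = 5.0 to 6.0 h, before any retraining.

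| Assumed c | Difference (5.0 − c to 6.0 − c) | Ratio (5.0/c to 6.0/c) |
|---|---|---|
| 0.5 h | 4.5 to 5.5 h | 10 to 12 |
| 1 h | 4.0 to 5.0 h | 5 to 6 |
| 2.5 h (mean tuina session, 5/2) | 2.5 to 3.5 h | 2.0 to 2.4 |
| 5 h | 0 to 1.0 h | 1.0 to 1.2 |

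The control session would need to last 5 h to equal the tuina training alone. Even then the type of contact would differ, because feedback, assessed performance and retraining would remain on one side only.

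**Step 3. Effect of shared contact.** If reminders go to both arms, each family receives 2 × 8 = 16 of them over 8 weeks. Contact of s hours common to both arms leaves the difference in hours unchanged but shrinks the ratio to (5 + a + m + s)/(c + s). Since neither s nor c is stated, no single ratio can be defended.

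**Step 4. Is the gap acknowledged elsewhere?** The limitations in the Discussion cover lack of blinding, variation in parents' learning ability, and the fact that physical pressure at specific body sites is not isolated. Unequal staff contact is not among them.

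**The case against.** The best defence is that the sentence does not claim equal minutes. Both arms share WeChat help, apparently the reminders, three assessments with assessor guidance, logbooks and process questionnaires, and that common contact is a real basis for saying that some attention is controlled. The trial is a feasibility pilot. It describes itself as underpowered, plans confidence intervals, urges caution, and concedes that the specific effect of pressure is not tested.

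Most of this stands as mitigation, but it does not rescue the clause. Shared contact does not offset the extra components on the tuina side, and conceding that pressure is not isolated does not tell the reader that attention also differs. Caution about precision does not address bias.

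The defence does rule out some stronger readings:

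- **That tuina parents get many times more contact.** The length of the control session is missing, and the shared contact is not timed.
- **That both consultations are tuina-only.** The Discussion says they go to the subjects without naming an arm. The inclusion criteria ask all parents to be available for pattern identification, and randomization follows the baseline assessments, so the baseline visit may reach both arms.
- **That every tuina parent has a live individual assessment.** A submitted video is allowed.
- **That the home-practice times show a further imbalance.** Every other day for 56 days is 28 sessions. That gives 28 × 20 = 560 to 28 × 30 = 840 min for tuina, against at least 560 min for control with no ceiling. This is parent-child time, not staff contact, and it is roughly matched.

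**Conclusion.** The concern holds for the contact-time clause. As described, the arms are not matched on staff contact, and the imbalance favours tuina. That direction does not depend on the consultations or on any assumed duration: inspected practice with feedback, a practitioner's assessment and retraining until competent have no described counterpart in the control arm. The size cannot be derived from the document, and the hours in the working only illustrate the range.

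The parent-child interaction half of the same sentence is broadly supported by the similar home schedules and is not in dispute.

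A reader might infer that any SNAP difference in favour of tuina would be an artefact of attention. The document does not support that. It supports only that attention and expectation could account for an unknown part of the difference, and that the comparator does not remove that part. The feasibility aims are unaffected. What changes is how the preliminary effect may be interpreted and carried into the main trial.

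**What to change.** 1. In the Discussion, remove the contact-time clause from the sentence about non-specific effects. The parent-child interaction clause may stay.
2. Add unequal staff contact to the limitations, noting that parents are unblinded and rate the outcomes.
3. State that the between-group effect size is for the whole tuina package, including its training and practitioner contact, against the control package.
4. Have existing staff record contact per family in both arms (training, feedback, consultations, WeChat) and report it by arm, so that the main trial can match it or account for it.

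The first three changes are wording. The fourth adds a small recording burden. The treatments, the sample size and the planned models stay as they are. The cost to the authors is a weaker claim about what the comparator controls.

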## Access to data

Researchers from Hong Kong Polytechnic University and Shandong University of Traditional Chinese Medicine Affiliated Hospital involved in this trial will have access to the final trial dataset.

## Dissemination

Dissemination of the results of the study will be carried out via submitting to the peer-reviewed journals, presenting on academic workshops and conferences, providing online or face-to-face courses for parents, and demonstrating the results on social media sites.

## Study status

The trial protocol was approved on 18 September 2019 and registered in ClinicalTrial.gov (NCT04237259) on 14 February 2020 (Additional file 2). The trial is currently open for recruitment. The study will be tracked by the ethics committee of Shandong University of Traditional Chinese Medicine Affiliated Hospital and the Departmental Research Committee of the Hong Kong Polytechnic University, and will be audited every 12 months.

## Data Availability

Not applicable.

## Abbreviations

ADHD: Attention deficit hyperactivity disorder
AAP: American Academy of Pediatrics
TCM: Traditional Chinese medicine
CMT: Congenital muscular torticollis
RCT: Randomized controlled trials
SNAP: Swanson, Nolan, and Pelham
CONSORT: Consolidated Standards of Reporting Trials
TAU: Treatment as usual
SPIRIT: Standard Protocol Items: Recommendations for Interventional Trials
CRF: Case report form
CIFG: Comprehensive Intervention Fidelity Guide
PAS: Preschool anxiety scale
CSHQ: Children’s sleep habits questionnaire
PSS: Parental stress scale
